# Efficacy and safety of human umbilical cord-derived mesenchymal stem cells (hUC-MSC PLEB001) for the treatment of grade II–IV steroid-refractory acute graft-versus-host disease: a study protocol for a multicenter, randomized, double-blind, placebo-controlled, phase II trial

**DOI:** 10.1186/s13063-023-07305-0

**Published:** 2023-05-03

**Keywords:** Acute graft-versus-host disease, Mesenchymal stem cell, Steroid, Second-line therapy, Human umbilical cord, Protocol

## Abstract

**Background:**

Systemic corticosteroid therapy failure is quite common in patients with newly diagnosed acute graft-versus-host disease (aGVHD). Growing evidence has suggested that mesenchymal stem cell (MSC) therapy could be a promising treatment option for aGVHD due to its distinctive immunomodulating functions. However, there is a lack of randomized well-controlled clinical trials.

**Methods:**

This is a clinical trial protocol for a multicenter, randomized, double-blind, placebo-controlled phase II study. The aim of the trial is to evaluate the efficacy and safety of the administration of the human umbilical cord-derived MSC product hUC-MSC PLEB001 in patients with grade II–IV, steroid-refractory aGVHD. A total of 96 patients will be randomized 1:1 to receive MSC or placebo treatment twice per week for 4 weeks, in addition to second-line therapy according to institutional standards. Patients who achieve partial response (PR) at day 28 will be eligible to receive further infusions twice per week for an additional 4 weeks.

**Discussion:**

This study will evaluate the efficacy and safety of MSC therapy in patients who have failed first-line steroid treatment for grade II–IV aGVHD.

**Trial registration:**

Chinese Clinical Trial Registry (ChiCTR), ChiCTR2000035740. Registered on 16 August 2020.

**Supplementary Information:**

The online version contains supplementary material available at 10.1186/s13063-023-07305-0.

## Background

Allogeneic hematopoietic stem cell transplantation (allo-HSCT) is a potential cure for various hematologic diseases [1]. Acute graft-versus-host disease that involves the skin, liver, or gastrointestinal tract is one of the common complications following allo-HSCT, with an overall incidence of 30–50% [2]. Systemic glucocorticoids, i.e., 1–2 mg/kg methylprednisolone, have been considered the first-line therapy for newly diagnosed aGVHD [3, 4]. However, steroid refractoriness, including steroid resistance and steroid dependence, occurs in more than 40% of patients and is associated with dismal outcomes [5, 6].

The use of most second-line therapies for aGVHD has been off-label, including basiliximab, α1-antitrypsin, and extracorporeal photopheresis [7]. Overall survival of aGVHD is not improved by most second-line therapies [8] due to immunosuppression-associated infections. Ruxolitinib, a Janus kinase (JAK) inhibitor, was approved for the treatment of steroid-refractory aGVHD by the US Food and Drug Administration (FDA) in May 2019 [9, 10]. However, this drug failed to demonstrate a significant advantage in terms of overall survival (OS) and raised concerns of hematologic toxicity and virus reactivation [11].

Mesenchymal stem cell therapy, which was developed in 2004, offers a new option for the treatment of aGVHD with few side effects. In the allo-HSCT setting, MSCs have been found to be effective for GVHD via immunomodulation, such as inhibiting the proliferation of T cells, promoting the expansion of Treg cells, and regulating the production of soluble factors such as NO and IDO [12, 13]. In addition, HLA-DR is not expressed on MSCs, which show minimal risk of initiating an allogeneic immune response [14]. In 2004, for the first time, Le Blanc et al. treated a patient with grade IV refractory aGVHD involving the gut and liver by infusion of MSCs from a haploidentical donor [15]. In 2008, Le Blanc et al. reported a phase II multicenter prospective clinical trial. Fifty-five patients with grade II–IV steroid-refractory aGVHD received MSCs from HLA-identical sibling donors, haploidentical donors, or third-party HLA-mismatched donors. The results showed that 54.5% of patients achieved complete response, 16.4% showed improvement, and no patients experienced side effects during or after infusion. The complete responders demonstrated superior 2-year overall survival after transplantation (53% vs. 16%, *p* = 0.018) [16]. Since then, the number of studies applying MSCs to treat steroid-refractory aGVHD has increased rapidly. However, there were apparent inconsistencies in outcomes between these trials, which were related to variability in MSC sources, production methodology, and limitations in study design [17].

Hence, there is an urgent need for randomized controlled trials (RCTs) to confirm the effect of MSCs on steroid-refractory aGVHD. By December 2021, nine RCT studies had been registered on ClinicalTrials.gov or the WHO’s international clinical trial registration platform (ICTRP) [18]. In 2020, Kebriaei et al. reported a multicenter, randomized, phase 3, double-blind, placebo-controlled trial of MSCs for 260 steroid-refractory patients [19]. The study failed to meet its primary endpoint—there was no significant difference between the durable complete response (DCR) rate in patients treated with MSCs in comparison to those treated with placebo (35% vs. 30%, *p* = 0.42). The trial found that MSC treatment led to significantly improved overall response (OR, 55% vs. 26%, *p* = 0.05) and DCR rates (29% vs. 5%, *p* = 0.047) in patients with liver aGVHD. There was also a higher overall response rate in children treated with MSCs than in controls (64% vs. 23%, *p* = 0.05). However, this study design involved both pediatric and adult patients, leading to clinical heterogeneity. Another limitation of the study was the nonstandardized use of second-line agents across study units.

Therefore, we designed a prospective, randomized, double-blind, placebo-controlled, multicenter phase II clinical trial to evaluate the efficacy and safety of the human umbilical cord-derived MSC product hUC-MSC PLEB001 in patients with grade II–IV steroid-refractory aGVHD.

## Methods

### Trial design

This is a multicenter, randomized, double-blind, placebo-controlled, superiority, phase II trial (Chinese Clinical Trial Registry, ChiCTR2000035740) that will enroll patients with grade II–IV steroid-refractory aGVHD from 8 Chinese centers. The primary endpoint is the overall response rate (ORR) at day 28. A total of 96 patients will be randomly assigned at a 1:1 ratio to receive either MSCs or placebo in a double-blinded manner. To ensure the interests of the patients, both the MSC and placebo groups will receive conventional second-line therapy. The MSC group will receive an infusion of hUC-MSC PLEB001 at 1.0 × 10^6^ MSC/(kg of subject, adjusted body weight) twice a week for 4 weeks. The control group will receive placebo treatment at the same frequency. The treatment efficacy will be assessed on the 28th day after the first infusion in all patients. The treatment will be terminated if the patient reaches complete response (CR), no response (NR), or progression of disease (PD) on the 28th day. Patients who display PR at day 28 will receive further infusions twice per week for an additional 4 weeks. The total treatment period will last no more than 8 weeks.

The conventional second-line therapy for patients with steroid-refractory aGVHD includes basiliximab, ruxolitinib, mycophenolate mofetil, methotrexate, etc. Investigators from each center will ensure the consistency of indications, category, and administration of second-line therapies. If deterioration or rapid progression of aGVHD is observed, another second-line agent can be added to the trial treatment regimen.

The protocol and the proposed informed consent form (ICF) will be reviewed and approved by an independent ethics committee (EC) before the study starts. Eligible patients may only be enrolled in the study after providing written informed consent.

In addition, peripheral blood samples will be collected from patients for the detection of Treg and Th17 cell populations prior to and after the treatment. Additional consent for peripheral blood sample collection and detection will also be included in the informed consent form.

### Study procedures and assessment

Investigators will introduce the trial to patients, who will be shown video and advertisement sheets describing the main aspects of the trial. Before obtaining informed consent, investigators must provide sufficient explanation to ensure that patients understand the nature, scope, and consequences of the clinical trial.

This trial will include a 7-day screening period, a treatment period lasting 4 to 8 weeks, and a follow-up period. The follow-up will continue until death, withdrawal from the study, or 360 ± 15 days after the first infusion. The flowchart of the study is presented in Fig. 1, and the schedule of screening, intervention. and follow-up are shown in Table 1.

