Participants may withdraw from the study for any reason at any time. Investigators will make the best effort to evaluate patients based on visit 19 before they withdraw from the trial. Detailed reasons for withdrawal, concomitant medications, and adverse events will be recorded to obtain safety data for those who withdraw consent or are lost to follow-up.

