### Safety reporting

#### AE

Adverse events are collected through interrogation, physical examination, laboratory or other tests, and self-reporting. Investigators are required to collect AEs from the time of the first dose and continue to collect AEs until 180 days after the first infusion, death, or early withdrawal from the clinical study (whichever occurs first).

In this trial, the severity of adverse events is graded according to the common terminology criteria adverse events (CTCAE 5.0) published by the National Cancer Institute (NCI) [20]. The potential association between adverse events and investigational product will be examined based on the “Adverse Drug Reaction Reporting and Detection Workbook” issued by the National Adverse Drug Reaction Monitoring Centre.

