### Concomitant medication

Cyclosporine A, mycophenolate mofetil, and short-term methotrexate for aGVHD prophylaxis will be administered. Subjects may be given antibiotics to prevent or treat infections that occur after transplantation. In addition, subjects will be able to receive supportive therapy. No other trial agents or MSC products will be allowed within 30 days prior to and during the trial.

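### Survival and adverse-event collection stop at study withdrawal, so OS at days 100 and 180 and AE/SAE to day 180 may be biased if withdrawal is related to non-response

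*Protocol article*

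**What the plan says.** All references are to the protocol article.

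- **Study procedures and assessment** sets the end of follow-up: "The follow-up will continue until death, withdrawal from the study, or 360 ± 15 days after the first infusion".
- **Safety reporting, AE** tells investigators to "continue to collect AEs until 180 days after the first infusion, death, or early withdrawal from the clinical study (whichever occurs first". The SAE section says that SAEs are collected in the same way as AEs.
- **Text after Table 1:** "Participants may withdraw from the study for any reason at any time". For those who leave, "Investigators will make the best effort to evaluate patients based on visit 19 before they withdraw from the trial". Reasons, concomitant medication and adverse events are also to be recorded, but no period after withdrawal is mentioned.
- **Notes to Table 1** treat two groups differently. Patients who withdraw are assessed as at visit 19. Patients who deviate from the intervention or the visit schedule stay on the ordinary calendar. The table schedules survival status to visit 27 (day 360).
- **Study endpoints, Table 2** lists OS at days 100 and 180 as secondary endpoints and AE/SAE at day 180 as a safety endpoint.
- **Statistical analysis** applies worst observation carried forward to the primary endpoint only. Other missing values are left to the observed data.
- **Sample size** aims for 40 analysed per group, assumes 20% dropout and enrols 48 per group.

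**The concern.** These sections together fix what is gathered. Once a patient withdraws, the article provides for no further record of whether that patient lived or died, or of later SAEs. OS is a named endpoint at two later times, and no analysis can restore deaths that were never recorded.

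The loss would be harmless if withdrawal were unrelated to prognosis. In this population that is doubtful. A patient whose aGVHD has not responded has more reason to leave, and is also more likely to die, than one who has responded. If so, an analysis of observed data describes a group with better prognosis than the one randomized. Survival is overstated in each arm, and if withdrawal among non-responders differs by arm the comparison is distorted too. The same holds for SAEs up to day 180.

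**Working it through.** **The plan's own figure.** 40 × 1.20 = 48 per group, 96 in total, which reproduces the stated enrolment. The implied loss can be read in two ways: 48 − 40 = 8 per arm, or 0.20 × 48 = 9.6, about 10 per arm. The article does not split dropout by cause, timing or response.

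**Model for selective loss.** Let p be the day-28 response rate, sR and sN the day-180 survival of responders and non-responders, and w the share of non-responders who withdraw.

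- True OS = p·sR + (1 − p)·sN
- Observed-case OS = [p·sR + (1 − p)(1 − w)·sN] / [p + (1 − p)(1 − w)]

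The model takes withdrawing non-responders to have the same survival as other non-responders and drops them entirely. None of p, sR, sN and w is in the article. The assumed ranges are p = 0.4 to 0.6, sR/sN = 0.7/0.3 or 0.8/0.2, and w = 10% to 40%.

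**Level in one arm.** Example with p = 0.5, sR/sN = 0.7/0.3, w = 0.4:

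- True: 0.5 × 0.7 + 0.5 × 0.3 = 0.50
- Observed: (0.35 + 0.5 × 0.6 × 0.3) / (0.5 + 0.3) = 0.44 / 0.80 = 0.55
- Overstatement: 5 points

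| w | Overstatement of OS per arm, over the assumed ranges |
|---|---|
| 10% | about 1–2 points |
| 20% | about 2–3 points |
| 40% | about 5–8 points |

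**Between-arm difference, equal w.** Response 0.6 versus 0.4:

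| sR/sN | True difference | w = 20% in both arms | w = 40% in both arms |
|---|---|---|---|
| 0.7/0.3 | 8.0 points | 7.9 | 7.5 |
| 0.8/0.2 | 12.0 points | 11.9 | 11.3 |

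The shift is below 1 point in every case.

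**Between-arm difference, unequal w.** Same response rates, sR/sN = 0.7/0.3, true difference 8.0 points:

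- 10% withdrawing in the better arm, 40% in the other: (0.42 + 0.108)/0.96 = 0.550 and (0.28 + 0.108)/0.76 = 0.511. The difference is about 3.9 points, a shift of about −4.
- Reversed: (0.42 + 0.072)/0.84 = 0.586 and (0.28 + 0.162)/0.94 = 0.470. The difference is about 11.5 points, a shift of about +3.5.

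With sR/sN = 0.8/0.2 (true difference 12.0 points):

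- First pattern: 0.552/0.96 − 0.392/0.76 = 0.575 − 0.516, about 5.9 points (shift about −6).
- Reversed: 0.528/0.84 − 0.428/0.94 = 0.629 − 0.455, about 17.3 points (shift about +5).

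**Extreme bound.** Suppose k of 48 per arm are lost and the arms have equal numbers of known survivors. The true difference then lies within ±k/48: 8/48 = ±16.7 points, 10/48 = ±20.8 points. To reach the bound, every lost patient in one arm must die and every one in the other must live.

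**The case against.** A reader might infer a stronger chain. Patients without response stop infusions at day 28 ("The treatment will be terminated if the patient reaches complete response (CR), no response (NR), or progression of disease (PD) on the 28th day"). They remain in the trial to day 360, and meanwhile "No other trial agents or MSC products will be allowed within 30 days prior to and during the trial". On that reading they are driven to leave, so OS and late safety are lost selectively. The document does not support this:

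- No section says that taking a barred product leads to withdrawal. It would be a deviation. The notes to Table 1 keep patients who deviate on the calendar, and the section on protocol amendments asks only that deviations be documented and, if significant, reported.
- The incentive is narrow. On deterioration "another second-line agent can be added to the trial treatment regimen", so only other trial agents and MSC products are out of reach.
- What ends at day 28 is treatment, not participation. The day-28 rule, the follow-up rule and the restriction on other products do not contradict one another.
- AE collection ends at day 180 for everyone, so little late safety is at stake beyond that.

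The other side also has fair points on weight. The primary endpoint is at day 28, OS is secondary and the trial is exploratory. Deaths on study are observed. Blinding makes unequal withdrawal among non-responders less likely. The 20% dropout is a general allowance, so the ±17 to ±21 points is a generic missing-data bound and not an estimate of this bias. All of this stands, and it limits the size of the point.

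A last objection is that a condensed article may leave checks after withdrawal to the full protocol V6.0. That would carry weight if the article were silent. It states when follow-up and AE collection end, and withdrawal is one of those ends. If V6.0 provides for later record checks, the article should be brought into line with it.

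**Conclusion.** The point holds as a limited weakness in data collection. Under the stated rules, survival and SAEs after withdrawal are not gathered, and the observed-data rule for OS does nothing to offset this. If withdrawal is related to non-response, OS per arm would be overstated by about 1 to 8 points under the assumed ranges. The comparison would be nearly unaffected (under 1 point) with equal withdrawal among non-responders. It would move by about 4 points at an assumed 10% versus 40% with survival 0.7/0.3, and by 5 to 6 points with survival 0.8/0.2, in either direction.

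That selective loss will happen, or that the restriction on other products causes it, cannot be concluded from the document. Its size and direction cannot be set from the document either.

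**What to change.** Amend three places: the end-of-follow-up sentence in Study procedures and assessment, the withdrawal paragraph after Table 1, and the AE section.

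1. State that stopping infusions, or starting a non-permitted agent, is recorded with its date and does not by itself end follow-up. This matches the note to Table 1 on patients who deviate.
2. For patients who withdraw from visits, collect vital status to day 360 and SAEs to day 180 from hospital records or by telephone.
3. Let only an explicit refusal of further data collection end this, and say so in the consent form.
4. For patients who have already withdrawn, seek vital status from hospital records where their consent allows.

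The cost is some protocol and consent wording and slight extra work at the sites. The collection would remove the survival bias described here, except for patients who refuse it or cannot be traced. No change to the restriction on other trial agents and MSC products is proposed.

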**Fig. 1 Fig1:**
[figure not shown]
Flowchart of the study

**Table 1 Tab1:** Schedule of screening, intervention, and follow-up

Stage		Screening	Treatment																		Follow-up			
**Visit**		**Visit 1**	**Visit 2**	**Visit 3**	**Visit 4**	**Visit 5**	**Visit 6**	**Visit 7**	**Visit 8**	**Visit 9**	**Visit 10**	**Visit 11**	**Visit 12**	**Visit 13**	**Visit 14**	**Visit 15**	**Visit 16**	**Visit 17**	**Visit 18**	**Visit 19**	**Visits 20–24**	**Visit 25**	**Visit 26**	**Visit 27**
**Time (day)**		** − 14 ~ 0**	**1**	**4 ± 1**	**8 ± 1**	**11 ± 1**	**15 ± 1**	**18 ± 1**	**22 ± 1**	**25 ± 1**	**28 ± 1**	**29 ± 1**	**32 ± 1**	**36 ± 1**	**39 ± 1**	**43 ± 1**	**46 ± 1**	**50 ± 1**	**53 ± 1**	**56 ± 1**	**63 ± 3, 70 ± 3, 77 ± 3, 84 ± 3, 91 ± 3**	**100 ± 3**	**180 ± 7**	**360 ± 15**
**Time (week)**		**0**	**W1**	**W1**	**W2**	**W2**	**W3**	**W3**	**W4**	**W4**	**W4**	**W5**	**W5**	**W6**	**W6**	**W7**	**W7**	**W8**	**W8**	**W8**	**W9, W10, W11, W12, W13**	**W14**	**W26**	**W52**
Informed consent		**X**																						
Demographic data		**X**																						
Medical history		**X**																						
Vital signs		**X**	**X**	**X**	**X**	**X**	**X**	**X**	**X**	**X**	**X**	**X**	**X**	**X**										
Randomization		**X**													**X**	**X**	**X**	**X**	**X**	**X**	**X**	**X**	**X**	
Colonoscopy		**X**																						
Physical exam		**X**									**X**									**X**				
Height/weight		**X**	**X**	**X**	**X**	**X**	**X**	**X**	**X**	**X**	**X**	**X**	**X**	**X**	**X**	**X**	**X**	**X**	**X**	**X**				
Laboratory test^a^	CBC	**X**	**X**	**X**	**X**	**X**	**X**	**X**	**X**	**X**	**X**	**X**	**X**	**X**	**X**	**X**	**X**	**X**	**X**	**X**				
	Comprehensive metabolic panel	**X**	**X**	**X**	**X**		**X**		**X**		**X**		**X**		**X**		**X**			**X**	**X**	**X**		
	CRP	**X**																						
	Coagulation	**X**		**X**	**X**		**X**		**X**		**X**									**X**				
	Blood type	**X**																						
	HBV, HCV, TP, HIV serostatus	**X**			**X**		**X**		**X**		**X**		**X**		**X**		**X**			**X**				
	CMV-DNA	**X**			**X**		**X**		**X**		**X**		**X**		**X**		**X**			**X**				
	EBV-DNA	**X**			**X**		**X**		**X**		**X**		**X**		**X**		**X**			**X**				
	Urinalysis	**X**	**X**	**X**	**X**		**X**		**X**		**X**		**X**		**X**		**X**			**X**				
	Fecal analysis and OBT	**X**	**X**	**X**	**X**		**X**		**X**		**X**		**X**		**X**		**X**			**X**				
12-leads ECG^a^		**X**									**X**									**X**				
Abdominal ultrasound scan^a^		**X**									**X**									**X**				
Th17 and Treg count (prior to MSC infusion)			**X**				**X**				**X**									**X**				
CEA, CA125, CA199, AFP^a^		**X**									**X**									**X**				
X-ray or CT of chest		**X**									**X**									**X**				
Gastrointestinal examination		**X**		**X**	**X**		**X**		**X**		**X**		**X**		**X**		**X**			**X**	**X**	**X**		
Cutaneous examination		**X**		**X**	**X**		**X**		**X**		**X**		**X**		**X**		**X**			**X**	**X**	**X**		
aGVHD evaluation^1^		**X**		**X**	**X**		**X**		**X**		**X**		**X**		**X**		**X**			**X**	**X**	**X**		
ECOG score		**X**									**X**									**X**		**X**		
Pregnancy test( for female of child bearing potential)		**X**									**X**									**X**				
SaO2/SAT^2^		**X**	**X**	**X**	**X**	**X**	**X**	**X**	**X**	**X**		**X**	**X**	**X**	**X**	**X**	**X**	**X**	**X**					
Inclusion/exclusion criteria		**X**																						
Intervention			**X**	**X**	**X**	**X**	**X**	**X**	**X**	**X**		**X**	**X**	**X**	**X**	**X**	**X**	**X**	**X**					
AEs			**X**	**X**	**X**	**X**	**X**	**X**	**X**	**X**	**X**	**X**	**X**	**X**	**X**	**X**	**X**	**X**	**X**	**X**	**X**	**X**	**X**	
Concomitant disease and medication		**X**	**X**	**X**	**X**	**X**	**X**	**X**	**X**	**X**	**X**	**X**	**X**	**X**	**X**	**X**	**X**	**X**	**X**	**X**	**X**	**X**	**X**	
Medical recording of aGVHD after investigational product																					**X**	**X**	**X**	
Imaging of secondary tumors																						**X**	**X**	**X**
Survival status			**X**	**X**	**X**	**X**	**X**	**X**	**X**	**X**	**X**	**X**	**X**	**X**	**X**	**X**	**X**	**X**	**X**	**X**	**X**	**X**	**X**	**X**

Subjects who withdraw from the trial should be assessed according to visit 19

Detailed information about the test items is shown in the clinical trial protocol V6.0, which could be provided by the trial sponsor

1. According to the modified Glucksberg criteria

2. Monitoring with a pulse oximeter at least 30 min before MSC infusion to 2 h after infusion

^a^Test results prior to randomization are acceptable during the screening period, and the exact time limits are described in the clinical trial protocol V6.0

Subjects who deviate from intervention protocols or the follow-up schedule of assessments will follow the same calendar as those with good compliance, except adherence assessment.

Participants may withdraw from the study for any reason at any time. Investigators will make the best effort to evaluate patients based on visit 19 before they withdraw from the trial. Detailed reasons for withdrawal, concomitant medications, and adverse events will be recorded to obtain safety data for those who withdraw consent or are lost to follow-up.

